##### Stage 1b (Not Mandated): Thoracoscopic LAA Exclusion

Once epicardial ablation is completed, the subject may proceed to LAA exclusion. LAA exclusion will be performed via a video‐assisted thoracoscopic surgical approach using a 3‐port thoracoscopy (2‐ to 3‐mm port in the second intercostal space in the midclavicular line, a 5‐mm port in the fourth intercostal space along the midaxillary line, and a 12‐mm port in the sixth intercostal space in the posterior axillary line). The left lung will be deflated to visualize the pericardial sac, and the pericardium will be opened using a LigaSure device (Medtronic, Minneapolis, MN). The LAA will be identified and measured using a dedicated AtriCure device before deployment of the AtriClip Pro device. Occlusion at the base of the LAA will be confirmed by transesophageal echocardiography before final device deployment. If LAA exclusion is performed, a drain will be placed in the pleural cavity via the lowest port. Any HA cases where LAA exclusion is performed will be prospectively recorded and reported descriptively.

##### Stage 2: Percutaneous Endocardial CA to achieve PVI and PWI

The endocardial component of the convergent procedure (stage 2) will be performed during a separate admission ≈8 to 16 weeks after stage 1, where possible. The procedure follows the same transseptal approach as the CA‐only procedure. As per the comparator arm, endocardial ablation may use thermal (RFA) or nonthermal (PFA) energy sources. A baseline EAM will be created to assess the ablation performed at stage 1. Supplementary endocardial ablation will be administered to achieve PVI and PWI. Confirmation of block or isolation after ablation will follow the CA arm protocol (including assessment of local electrograms and pacing maneuvers to demonstrate block and, where applicable, creation of a post‐PFA EAM). Any areas of residual electrical activity or gaps will be targeted with supplementary ablation until isolation is confirmed or deemed not technically achievable. As with the CA arm, procedural details, including energy source, mapping system, lesion sets, procedure duration, confirmation of isolation, and acute procedural outcomes, will be recorded prospectively. Acute procedural success of HA will be defined as confirmation of PVI and PWI following stage 2. The endocardial lesion sets for stage 2 HA are specified below:

RFA (point‐by‐point RFA guided by ablation‐index or high‐power short‐duration protocols under EAM guidance)
Antral PVI (wide area circumferential catheter ablation lesions as needed to complete PVI)Linear ablation comprising a complete or partial roof and floor line (as required, depending on ablation at stage 1) to achieve PWIMapping and ablation of any atrial tachycardia that occurs during the procedure

PFA (pentaspline PFA catheter under EAM guidance)
Antral PVI: individual isolation of each PV (as needed) with a combination of flower and basket lesionsOverlapping lesions across the PW (as needed) to achieve PWIMapping and ablation of any atrial tachycardia that occurs during the procedure

#### Ablation Strategy and Energy Source

RFA or PFA may be used for endocardial ablation in either treatment arm. While studies have suggested that PFA may enhance procedural efficacy and patient pathways, randomized comparisons and meta‐analyses have not consistently shown it to be superior to thermal ablation in terms of freedom from recurrent arrhythmia.^47^, ^48^, ^49^ Importantly, energy modalities are not the object of comparison in HALT AF. Rather, the trial is designed to compare ablation strategies, namely, epicardial–endocardial ablation versus endocardial‐only ablation, and to determine whether the addition of an epicardial lesion set confers incremental benefit over endocardial ablation alone, irrespective of endocardial energy modality. Accordingly, the protocol mandates identical electrophysiological procedural end points in both arms, comprising confirmation of PVI and PWI, irrespective of the endocardial energy source, with randomization strictly preserved at the strategy level. Acute procedural success, defined as electrophysiological confirmation of PVI and PWI at the conclusion of the procedure, will be prospectively recorded in all cases to verify end point achievement across arms. Ablation energy use will be reported transparently and evaluated in prespecified exploratory analyses to assess whether strategy‐level treatment effects appear consistent across endocardial energy modalities. These analyses are descriptive and hypothesis generating only, and the study is not powered to compare outcomes between PFA and RFA or to support inference about energy‐source superiority or procedural sequencing.

#### Postprocedure Care and Anticoagulation (Both Arms)

All patients will receive standard postprocedural care in accordance with local institutional protocols. Patients will be advised that they will be admitted and monitored overnight for complications. Anticoagulation will resume on the day of the procedure unless clinically contraindicated. Patients who have had a drain sited following LAA exclusion will have it removed, and all patients will be discharged the following day after a focused echocardiogram and on their usual medications, unless there is an indication for a longer admission. Same‐day discharge will be permitted following adequate monitoring and imaging, in accordance with local best‐practice protocols and patient choice. AADs (class I/III) may be continued or initiated in the early postoperative period. However, all class I or class III AADs will be discontinued by 3 months after ablation in both arms (at the end of the blanking period). Patients will be closely followed up postoperatively with early review under the nurse‐led postablation service. All patients will be provided with the research team's contact details and encouraged to contact them early if they notice any potential complications or have concerns.

#### Follow‐Up Schedule

To ensure methodological equivalence across treatment strategies, efficacy follow‐up is anchored to a harmonized time point (T_0_), defined as the date on which each participant has completed the analogous intended lesion set (PVI plus PWI), which represents completion of the randomized ablation strategy. In the CA arm, T_0_ occurs at the index procedure; in the hybrid arm, T_0_ occurs following completion of stage 2. This strategy‐level framework ensures that rhythm outcomes are assessed only after the equivalent lesion set has been delivered in both arms and avoids misclassification due to incomplete or partial procedures. All clinical events occurring between stage 1 and stage 2 in the hybrid arm will be prospectively captured, adjudicated, and included in secondary and safety analyses. Variation in the timing of stage 2, therefore, affects only the scheduling of post‐T_0_ assessments and does not alter the definition of the primary efficacy analysis. This design constitutes a prespecified postcompletion (T_0_‐anchored) efficacy framework and is not intended to estimate treatment effects from the time of randomization. Participants who do not complete stage 2 will remain included in the primary binary efficacy analysis within the modified intention‐to‐treat population. For these participants, T_0_ will be assigned as the protocol‐scheduled stage 2 time point, defined as 3 months after stage 1. Primary end point status will be classified according to the prespecified end point definitions using available postrandomization data on rhythm and AAD use. Noncompletion of stage 2 will be recorded and incorporated into end point adjudication and sensitivity analyses in accordance with the prespecified analysis plan.

The follow‐up schedule and tests are detailed in Table 1. Follow‐up will consist of 3 scheduled reviews (at 3, 6, and 12 months after T_0_). At each visit, clinical and rhythm status will be assessed, and cardiac function will be evaluated at prespecified time points. Scheduled evaluation will include a 12‐lead ECG, a 7‐day ambulatory ECG monitor (at 6 and 12 months), echocardiography (at 6 and 12 months), blood tests, clinical assessment, and quality‐of‐life assessments. Blood tests at baseline and follow‐up will include NT‐proBNP (N‐terminal pro‐B‐type natriuretic peptide), CRP (C‐reactive protein), lipid profile, renal function, and complete blood count. To ensure consistency across centers, each time point will include an allowable visit window. Out‐of‐window assessments will be documented and may contribute to supportive or sensitivity analyses; however, they will not replace the prespecified time point in the primary analysis. Where they document a qualifying recurrence after blanking, they may contribute to end point adjudication, but they do not substitute for scheduled windowed assessment. Further information on the visit plan and data collection is provided in Table 1. Unscheduled follow‐up and investigations may be initiated at any time if symptoms or clinical concerns arise that suggest a complication or recurrence of arrhythmia. The findings will be recorded and included in end point adjudication, but they will not substitute for scheduled visits unless they fall within the prespecified window. All investigations will be conducted by clinicians and technicians blinded to the patient's assigned arm, with analysis performed separately from the clinical encounter and adjudicated blindly.

**Table 1 jah370697-tbl-0001:** Visit Plan and Data Collection Schedule for HALT AF

	Baseline	3‐mo	6‐mo	12‐mo
Visit window (T_0_+),* d	…	90±14	180±21	365± 30
Eligibility criteria	X			
Informed consent	X			
Randomization	X			
Baseline demographics	X			
Optimization of medical therapy for AF and HF	X	X	X	X
Medical history, including medications, symptom score, and need for any admission or rhythm control	X	X	X	X
Clinical examination	X	X	X	X
12‐lead ECG	X	X	X	X
Blood tests†	X	X	X	X
Echocardiography	X		X	X
EQ‐5D‐5L	X		X	X
MLHFQ	X		X	X
AFEQT	X		X	X
Adverse event review		X	X	X
7‐d Holter monitor			X	X

AF indicates atrial fibrillation; AFEQT, Atrial Fibrillation Effect on Quality‐of‐Life Questionnaire; EQ‐5D‐5L, EuroQol 5‐Dimension 5‐Level questionnaire; HALT AF, Hybrid Ablation for Atrial Fibrillation With Heart Failure; HF, heart failure; MLHFQ, Minnesota Living With Heart Failure Questionnaire; and T_0_, harmonized time point.

* T_0_ = completion of the intended lesion set: pulmonary vein isolation and posterior wall isolation.

^†^
Blood tests include N‐terminal pro‐B‐type natriuretic peptide, C‐reactive protein, renal function, complete blood count, and lipid profile.

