Isolation will be validated in all cases by assessing local electrograms and performing pacing maneuvers to detect electrical block. For PFA procedures, a postablation EAM will also be created to evaluate for residual electrical activity. Areas of reconnection or gaps will be targeted with supplementary ablation until isolation is complete or deemed impossible to achieve. Procedural details, including energy source, mapping system, lesion sets, ablation duration, confirmation of isolation, and acute procedural outcomes, will be documented prospectively. Acute procedural success will be defined as the achievement of PVI and PWI at the end of the procedure.

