### Efficacy End Points

#### Primary End Point

The primary efficacy end point is freedom from any atrial arrhythmia (defined as AF, atrial flutter, or atrial tachycardia lasting >30 seconds) off class I or III AADs through 12 months after T_0_ (completion of the intended ablation lesion set). The primary end point is evaluated from the end of a 3‐month blanking period. Recurrence may be detected on any of the following methods during scheduled or unscheduled symptom‐driven encounters and is considered met on first documentation, irrespective of frequency or symptom status.
12‐lead ECGRhythm strip7‐day Holter monitor (or any Holter >24 hours if arranged via usual clinical care)Device interrogation (where applicable)

For participants who complete the intended ablation lesion set, follow‐up timing is anchored to T_0_. Participants who undergo partial delivery of their allocated ablation strategy but are unable to complete the intended lesion set for any reason (including persistent LA thrombus precluding hybrid stage 2 or procedural complications) will remain included in the primary efficacy analysis within the prespecified modified intention‐to‐treat analysis set and end point definitions. All interstage events and procedural exposures in the hybrid arm will be prospectively captured within safety and secondary analyses. For the 12‐month binary rhythm end point, these participants will be classified on the basis of their observed rhythm status, antiarrhythmic drug use, cardioversion, and repeat ablation status, using the same end point definitions as for participants who reach T_0_. Cardioversion or repeat ablation for arrhythmia recurrence occurring after the blanking period will be considered a treatment failure for the binary rhythm end point.

Patients who demonstrate no recurrence of qualifying arrhythmia and do not require cardioversion or repeat ablation after the blanking period are considered treatment successes with respect to efficacy.

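### T0 is stated two ways, leaving patients whose procedure ends without PVI plus PWI with no consistent start of follow-up

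*Protocol article*

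**What the plan says.** The protocol article anchors efficacy follow-up to T0 and describes it in two ways.

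- **By lesion set.** The Follow-Up Schedule says T0 is "defined as the date on which each participant has completed the analogous intended lesion set (PVI plus PWI"). The Table 1 footnote repeats this: "completion of the intended lesion set: pulmonary vein isolation and posterior wall isolation". The Primary End Point section anchors timing to T0 "For participants who complete the intended ablation lesion set". It then describes those who could not complete the set, whatever the reason, and contrasts them with participants who reach T0.
- **By procedure.** The Follow-Up Schedule continues: "In the CA arm, T_0_ occurs at the index procedure; in the hybrid arm, T_0_ occurs following completion of stage 2". No condition on the acute result is attached.

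The protocol expects some procedures to end without isolation. In the CA arm, "Areas of reconnection or gaps will be targeted with supplementary ablation until isolation is complete or deemed impossible to achieve". At hybrid stage 2, ablation continues "until isolation is confirmed or deemed not technically achievable". The Primary End Point section also names procedural complications as a reason for non-completion.

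One substitute date exists. Hybrid patients who do not complete stage 2 are assigned the scheduled "stage 2 time point, defined as 3 months after stage 1".

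Blanking (Blanking Period), the 3-, 6- and 12-month visits (Table 1) and the T0+365±30 day assessment (Primary Efficacy Analysis, Missing Data) all depend on T0. The Primary Efficacy Analysis limits the time-to-event analyses to participants who reach T0.

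**The concern.** The two descriptions agree only if every CA procedure and every stage 2 achieves PVI plus PWI, and the protocol says that this may not happen. Where isolation fails, one description gives a date and the other gives none.

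Two things are at stake. First, these patients are kept in the binary primary analysis, where an arrhythmia or cardioversion counts only after blanking, yet blanking has no agreed start for them. Second, whether they enter the key supportive time-to-event analysis depends on which description is followed. On the lesion-set reading, entry depends on acute procedural success, which is observed after randomization and may be related to recurrence.

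**Working it through.** **Step 1: the plan's sample size, for reference.** Inputs from Sample Size Estimation and Statistical Threshold: 70% vs 43%, two-sided alpha 0.05, 80% power, 1:1. With pooled variance under the null and mean proportion 0.565:

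n = [1.960 × √(2 × 0.565 × 0.435) + 0.842 × √(0.70 × 0.30 + 0.43 × 0.57)]² / 0.27² ≈ 3.77 / 0.0729 ≈ 51.7, so 52 per arm.

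This matches the stated 52 per arm (104 in total). 104 × 1.15 = 119.6, which matches 120. Neither figure depends on how T0 is defined.

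**Step 2: apply each description to each type of patient.**

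| Patient | By lesion set | By procedure | Assigned T0 applies? |
|---|---|---|---|
| CA, PVI achieved, PWI not | none | index procedure | no |
| CA, procedure aborted | none | index procedure | no |
| Hybrid, stage 2 done, isolation not achieved | none | stage 2, if that counts as completing it | not clearly |
| Hybrid, stage 2 not completed | none | none | yes, 3 months after stage 1 |

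Only the last row is settled by an explicit rule. Hybrid non-completers of stage 2 receive a date, while CA non-completers receive none under the lesion-set description.

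**Step 3: follow one patient through.** Take a CA patient with PVI but no PWI and AF documented just over 90 days after the procedure. By procedure, the AF falls after blanking. It is a failure in the binary analysis and an event in the Cox model. By lesion set, there is no T0. The patient stays in the binary analysis (Primary End Point, Statistical Analyses) but without a dated end of blanking, and is outside the main time-to-event analysis.

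**Step 4: size in the supportive set.** The article gives no acute failure rate, so the share *f* of CA patients affected is an assumption. Suppose that all of them recur and are dropped, and use the planning proportions as a stand-in for the time-to-event result. CA success among the rest is then 0.43 / (1 − f).

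| f | CA patients of 60 | CA success among the rest | Difference from 70% |
|---|---|---|---|
| 2% | 1.2 | 43.9% | 26.1 points |
| 5% | 3 | 45.3% | 24.7 points |
| 10% | 6 | 47.8% | 22.2 points |
| 15% | 9 | 50.6% | 19.4 points |

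With only CA patients dropped, the shift works against the hybrid arm. The direction is not fixed. If 5% of each arm were dropped on the same terms, hybrid success would be 0.70 / 0.95 = 73.7%, and the difference 73.7 − 45.3 = 28.4 points.

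**The case against.** The best reply is that the by-arm sentence already supplies a usable date. It follows the definition directly and carries no condition on the result. The Blanking Period section also counts its 90 days from the procedure. The definition speaks of completing a lesion set, and electrophysiological confirmation is recorded separately as acute procedural success, so T0 could be read as the end of the last planned procedure. The article is also condensed, and the analysis plan, which is not shown, may settle such cases.

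Much of this stands. A site would probably use the index date, and the number affected may be small. It does not remove the conflict, because the Primary End Point section sets those unable to complete the lesion set apart from those who reach T0, in wording not limited to the hybrid arm. The Follow-Up Schedule justifies the framework as protection against misclassification from incomplete or partial procedures. The Per-Protocol Analysis treats lesion-set completion as a requirement beyond receiving the allocated strategy. These statements are in the article itself and are not details left to the analysis plan.

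A reader might infer more than this, and three such inferences fail.

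- **A later redo moves T0 and erases earlier recurrences.** Management of Arrhythmia Recurrence counts any repeat ablation as failure of the binary end point and says that it does not reset the time-to-event timing.
- **These patients drop out of the primary analysis.** The Primary End Point and Statistical Analyses sections keep everyone with partial delivery, in either arm.
- **The losses fall mainly in the CA arm.** No data support this, and the one arm-specific example of non-completion, LA thrombus precluding stage 2, is hybrid.

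**Conclusion.** The inconsistency is real and lies in the current text. The Follow-Up Schedule definition, the Table 1 footnote and the Primary End Point section tie T0 to lesion-set completion, while the by-arm sentence ties it to a procedure. Patients whose CA procedure or stage 2 ends without PVI plus PWI have no consistent T0.

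In the binary primary analysis the effect is an ambiguous start of blanking and of the 12-month window. It is not exclusion, and the documents do not allow its effect on the result to be quantified. In the supportive time-to-event analysis, the lesion-set reading excludes these patients on a post-randomization outcome. Under the assumptions that 2-15% of CA patients are affected, that all recur and that no hybrid patient is dropped, CA success in that set rises from 43% to about 44-51% and the difference falls from 27 to about 26-19 points. The range is illustrative. The wording should be settled before outcomes are adjudicated, so that the reading is not chosen with the failures known.

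**What to change.** - In the Follow-Up Schedule, the Table 1 footnote and the Primary End Point section, define T0 as the date of the index catheter procedure (CA) or of the stage 2 procedure (hybrid), whether or not PVI plus PWI was confirmed.
- Keep the existing assigned T0 for hybrid patients who do not complete stage 2.
- In the Primary Efficacy Analysis, state that all patients with an actual or assigned T0, in both arms, enter the time-to-event analysis.

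Acute success is already recorded separately, and the per-protocol analysis already addresses patients who completed the lesion set, so neither needs to change. The cost is a wording change and a slightly wider time-to-event set. There are no extra visits or patients, and no sample-size figure changes.

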#### Blanking Period

The blanking period extends from T_0_ to 90 days after the procedure. Arrhythmias during the blanking period will be recorded but will not count toward failure of the primary end point. Blanking‐period arrhythmias will not reset follow‐up or affect end point timing.

#### Management of Arrhythmia Recurrence

Management of recurrent arrhythmias will be in accordance with standard clinical care. A recurrence of arrhythmia within the 3‐month blanking period will be managed with medical therapy and electrical cardioversion as indicated. Repeat ablation is not clinically indicated nor permitted during the blanking period. Any recurrence during the blanking period will be documented but will not constitute a failure of the primary outcome. Arrhythmia recurrence occurring after the blanking period will be managed by optimizing medications for AF and HF, admission if required, and rhythm control via external cardioversion and repeat or “redo” ablation as indicated. Electrical cardioversion may be undertaken for symptomatic atrial arrhythmia or hemodynamic compromise, and all cardioversions will be recorded with the rhythm documentation supporting the indication.

Percutaneous CA will be the primary repeat procedure for patients in both treatment arms and will be discussed and offered to all patients with recurrence, as clinically indicated. As a general principle, redo ablation should be supported by objective documentation of rhythm and the persistence of arrhythmia despite appropriate medical therapy, unless urgent intervention is clinically required. The decision to proceed with repeat ablation will be documented, including evidence of rhythm, symptom burden, and relevant clinical factors, with all such events recorded and incorporated into end point classification to minimize center‐level bias. Repeat epicardial AF ablation is not indicated for any patient who has already undergone stage 1 HA, given the risks of pericardial adhesions and repeat epicardial access following the index procedure. Epicardial ablation (stage 1 HA) may be offered to patients in the CA arm (crossover) if AF recurrence persists despite a primary redo procedure following a further multidisciplinary team discussion. A repeat ablation of any type will be considered as treatment failure for the 12‐month binary primary rhythm end point. Repeat ablation will not reset the timing of the primary time‐to‐event analysis, which is defined as the time to the first documented recurrence. Rates and timing of cardioversion and repeat ablation will be reported as secondary outcomes.

